To complement self-reports and utilize an objective assessment measure of risk behavior, we use biological assays to confirm HIV and STI status. We selected five STIs: syphilis, gonorrhea, chlamydia, trichomoniasis and mycoplasma as objective proxies of sexual risk behavior. The choice of these STIs was based on their high prevalence and incidence in this population and the availability of definitive treatment with a single-dose medication (which obviates STI medication treatment adherence and compliance issues). We also selected HCV to index drug-related risk behaviors. A clinical coordinator conducts biological testing in each project field office location. A complete description of test systems used is provided in Table 2.

**Table 2 Tab2:** Biotesting systems used

Infection	Testing specimen	Test system used	Sensitivity (95% CI^a^)	Specificity (95% CI^a^)
HIV	Finger stick (whole blood sample)	Alere Determine™ HIV-1/2 Ag/Ab Combo rapid test system [47]	99.9% (99.4–100.0%)	99.8% (99.5–99.9%)
Hepatitis C (HCV)	Dried blood spot	Murex anti-HCV (version 4.0) [48]	100% (94.79-100%)	99.88% (99.77–99.94%)
Syphilis	Dried blood spot	Murex ICE Syphilis [49]	100% (99.1–100%)	100% (99.2–100%)
Gonorrhea	Vaginal specimen	AmpliSense *N. gonorrhea*/*C. trahomatis*/*M. genitalium*/*T. vaginalis*-MULTIPRIME-FRT PCR [50]	N/A^b^	N/A^b^
Trichomoniasis	Vaginal specimen	AmpliSense *N. gonorrhea*/*C. trahomatis*/*M*. *genitalium*/*T. vaginalis*-MULTIPRIME-FRT PCR [50]	N/A^b^	N/A^b^
Chlamydia	Vaginal specimen	AmpliSense *N. gonorrhea*/*C. trahomatis*/*M. genitalium*/*T. vaginalis*-MULTIPRIME-FRT PCR [50]	100% (73.3–100%)	100% (98.1–- 100%)
*Mycoplasma genitalium*	Vaginal specimen	AmpliSense *N. gonorrhea*/*C. trahomatis*/*M. genitalium*/*T. vaginalis*-MULTIPRIME-FRT PCR [50]	76.5% (50.1–93.0%)	100% (98.1–100%)

^a^CI confidence interval

^b^N/A estimates are not available for vaginal specimen samples

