Participants who test positive for any STI are provided with referrals and treatment. The clinical coordinator works with individual participants to ensure that they complete their course of treatment prior to randomization and session 1, ensuring that any STI acquired post randomization is an incidence STI, and, as soon as possible at follow-up, biotesting assessments. STIs acquired and treated between the baseline and month-9 assessment or between the month-9 and month-15 assessment at an external clinic are only included as an endpoint if it is self-reported by participants on their month-9 and month-15 assessments. The clinical coordinator refers participants who screen positive for syphilis to the local Skin and Venereal Disease Dispensary to receive additional confirmatory testing for syphilis, consultations with a physician, and treatment for active forms of syphilis. Treatment for HCV is not widely available in Kazakhstan, and clinical coordinators refer participants who test positive for HCV to specialized clinics for additional examination, monitoring, and treatment. Treatment for HIV is also limited in Kazakhstan. If participants receive a positive rapid test for HIV, the clinical coordinator refers them to the local AIDS center for confirmatory testing and treatment. HIV-positive participants sign an additional waiver allowing our study access to treatment records at the local HIV clinic. Clinical coordinators collect information on confirmatory testing (for newly diagnosed cases of HIV), viral-load test results, CD4 test results, and antiretroviral (ARV) medication history at every assessment period for each participant.

Participants receive the equivalent of US$10 for the baseline assessment, US$9 for the month-6 follow-up assessment, US$11 for the month-9 follow-up assessment, and US$16 for the month-15 follow-up assessment. The total possible reimbursements for assessments is US$46.

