### Data analysis

In assessing primary outcomes (STI, HIV, and HCV incidence, unprotected sexual acts and unsafe injection acts), our over-arching modeling approach estimates intervention differences (HIVRR alone versus HIVRR+MF) longitudinally using a generalized estimating equations (GEE) approach, a flexible extension of conventional regression models, to account for repeated measures and clustering imposed by randomizing individuals in groups of six to eight women per cohort. STIs will be summarized as both a count (number of positive test results for any of the five STIs of interest (syphilis, gonorrhea, chlamydia, trichomoniasis, mycoplasma)) over the entire follow-up period, as well as a binary indicator of a positive test for any STI of interest at each follow-up time. The primary analysis will be a logistic GEE (e.g., presence/absence of an incident STI post randomization), accounting for clustering imposed by the study design in having women receiving their randomized intervention in cohorts of six to eight women each. Additionally, secondary analyses will consider intervention effects on HIV and HCV incidence as operationalized by binary indicators of testing positive for either, respectively, over the entire follow-up. We will employ logistic (binary outcomes) and Poisson (count outcomes) GEE models to estimate intervention effects as appropriate. We will implement an intent-to-treat approach for all analyses. Model estimates will be presented as estimates of incidence risk ratios or odds ratios, as appropriate, and corresponding 95% confidence intervals (CIs) and *p* values will be calculated for inference. Additionally, a logistic GEE modeling approach will be implemented for dichotomous outcomes (e.g., GEE with specified logit link) when evaluating the following outcomes: (1) self-reported unprotected vaginal and anal sexual acts with both regular and paying partners and (2) self-reported unsafe injection acts. Again, we will be interested in estimate rate ratios or odds ratios comparing HIVRR+MF to HIVRR alone. A Poisson GEE modeling strategy (e.g., GEE with specified log link) will be implemented to evaluate remaining secondary outcomes (1) self-reported number of unprotected vaginal and anal sexual acts with both regular and paying partners and (2) self-reported number of unsafe injection acts. To evaluate the secondary aims of the study related to potential moderating effects, we will expand these models to include “moderator X intervention” interaction terms along with the corresponding main effects and will assess examine the significance of each moderator on intervention effects through these interaction terms.

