#### Power and sample size

Power and sample size considerations for this proposal prioritized sufficiently powering the study to detect intervention effects on incidence for the following biological outcomes: STIs (syphilis, gonorrhea, trichomoniasis, chlamydia, and mycoplasma), HIV and hepatitis C virus (HCV). Using baseline prevalence estimates from our prior work in similar populations (e.g., 10%, 28%, and 75%, for STIs, HIV, and HCV, respectively) [29], we conservatively focused on the least prevalent of the three biological outcomes of interest, STIs. We noted that if we were sufficiently powered to estimate intervention efficacy for the least prevalent outcomes, we would also be sufficiently powered to detect intervention effects for the others. Using these prevalence estimates, we determined a range of plausible incidences based on our experience in similar settings. We first calculated crude (unadjusted for clustering by cohort) using a conventional approach to detect differences in a binary outcome (e.g., incidence) in two groups assuming an *α*-level of 0.05 for a two-sided hypothesis test of an overall intervention effect. Crude sample size estimates were then inflated by the “variance inflation factor” as described in Donner and Klar [30], to account for the likely correlation of outcomes induced by the study’s cluster randomized design. Finally, we adjusted 20% attrition over the 15-month follow-up. We considered scenarios of modest (intraclass clustering coefficient (ICC) equal to 0.005) and moderate (ICC = 0.01) clustering effects. In summary, we determined that randomizing 350 women in equal proportions to each intervention (175 to HIVRR and HIVRR+MF) would ensure that 80% power to detect true relative risks of 0.25 and ICC = 0.01. This attrition and clustering adjusted sample size corresponds to detecting STI incidence relative risks (RR) equal to 0.25 comparing women randomized to HIVRR+MF to HIVRR alone, where the assumed STI incidence over the study follow-up period is 0.043 and 0.144, respectively. In these calculations, the assumed incidence in HIVRR alone of 0.144 represents a decrease of approximately 40% from the estimated baseline prevalence of 28% from our prior work in this population [29]. Because the other biological outcomes of interest are more prevalent, we expect to have greater than 80% power to detect similar intervention effects.

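### HIV and HCV incidence is coded as any positive follow-up test with no restriction to women negative at baseline, so existing infections count as new, and the power claim for these outcomes fails

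*Protocol article*

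**What the plan says.** The primary aim, in the opening of Methods/design, includes a lower rate of new HIV and HCV cases. The Data analysis section turns this into "HIV and HCV incidence as operationalized by binary indicators of testing positive for either, respectively, over the entire follow-up" and adds: "We will implement an intent-to-treat approach for all analyses". No sentence confines the HIV or HCV analysis to women who tested negative at baseline.

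The eligibility criteria contain no serostatus condition, and the Assessments section describes procedures for HIV-positive participants. Table 2 lists an anti-HCV assay and an HIV antigen/antibody rapid test. Table 1 schedules both at baseline, month 9 and month 15.

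The Power and sample size section lists expected baseline prevalences of 10% (STIs), 28% (HIV) and 75% (HCV). It argues that power for HIV and HCV will exceed 80% because they are more prevalent than STIs.

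The STIs are handled differently. Baseline infections are to be treated before randomization, "ensuring that any STI acquired post randomization is an incidence STI", and the primary analysis is of an incident STI. For syphilis, women who screen positive are referred for confirmation and "treatment for active forms of syphilis". The Data analysis section also describes the STI indicator as a positive test for any of the five infections at each follow-up.

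**The concern.** A woman who is HIV- or HCV-positive at baseline and again at month 9 meets the written definition of an incident case, although nothing happened to her after randomization. For the STIs, treatment before randomization is meant to prevent this. For HIV and HCV there is no such step, and the article itself says treatment for both is limited in Kazakhstan.

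These women become events in both arms at about the same rate. They add no information on the intervention and pull the relative risk towards 1. A null HCV result would then mostly reflect baseline prevalence, yet could be read as no effect on new infections.

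The power argument repeats the confusion. For a persistent infection, higher baseline prevalence leaves fewer women at risk of a new one, so it lowers power.

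**Working it through.** **Inputs from the Power and sample size section**
- Alpha: "level of 0.05 for a two-sided hypothesis test of an overall intervention effect".
- Target: "80% power to detect true relative risks of 0.25 and ICC = 0.01".
- Incidences: "the assumed STI incidence over the study follow-up period is 0.043 and 0.144, respectively" (HIVRR+MF first). The ratio is 0.043/0.144 = 0.30, so 0.30 is used as the true relative risk below.
- 175 women per arm and 20% attrition, so 140 per arm retained.
- Cohort size 7 (350 women in about 50 cohorts): design effect 1 + (7 − 1) × 0.01 = 1.06.

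**Reproducing the plan's figure.** The two-proportion formula (pooled variance under the null, no continuity correction) gives 130 per arm for 0.144 vs 0.043. Then 130 × 1.06 / 0.8 = 172.25, or 346 in total against the stated 350. Cohorts of 6 and 8 give 342 and 348. Power at 140 per arm with design effect 1.06 is 80.9%. The method is therefore a fair basis for what follows.

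**Assumptions**
- The article gives no HIV or HCV incidence. Two pairs are used among women negative at baseline: the STI pair 0.144 vs 0.043, and a lower pair 0.05 vs 0.015.
- HIV prevalence is run at 28% and at 10%, because the same section later attaches 28% to STIs.
- Women positive at baseline are taken to test positive again.

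**Risk under the written rule.** Observed risk = prevalence + (1 − prevalence) × incidence.
- HCV: 0.75 + 0.25 × 0.144 = 0.786 vs 0.75 + 0.25 × 0.043 = 0.761; RR 0.97.
- HIV at 28%: 0.28 + 0.72 × 0.144 = 0.384 vs 0.28 + 0.72 × 0.043 = 0.311; RR 0.81.
- HIV at 10%: 0.10 + 0.90 × 0.144 = 0.230 vs 0.10 + 0.90 × 0.043 = 0.139; RR 0.60.

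For HCV, 140 control women would yield 140 × 0.75 = 105 existing infections and only 35 × 0.144 ≈ 5 new ones.

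| Outcome | Incidence pair | RR as written | Power as written | At risk per arm | Power, baseline-negative only |
|---|---|---|---|---|---|
| HCV, 75% | 0.144 / 0.043 | 0.97 | 7% | 35 | 29% |
| HIV, 28% | 0.144 / 0.043 | 0.81 | 24% | 101 | 67% |
| HIV, 10% | 0.144 / 0.043 | 0.60 | 48% | 126 | 77% |
| HCV, 75% | 0.05 / 0.015 | 0.99 | 4% | 35 | 12% |
| HIV, 28% | 0.05 / 0.015 | 0.92 | 7% | 101 | 27% |
| HIV, 10% | 0.05 / 0.015 | 0.78 | 12% | 126 | 33% |

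Power counts rejections in the favourable direction only, which is why one entry is below 5%.

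**Size needed for 80% power in baseline-negative women, STI incidences.** Per arm, 172.25 / (1 − prevalence), rounded up, then doubled: HCV 689 per arm, 1,378 in total; HIV at 28%, 240 per arm, 480 in total; HIV at 10%, 192 per arm, 384 in total.

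**Syphilis in the STI composite, illustration only.** If an assumed share s of women stay screen-positive without a new infection, the same formula with s in place of prevalence gives RR 0.39 (power 73%) at s = 2%, 0.49 (62%) at 5% and 0.60 (48%) at 10%.

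**The case against.** The strongest defence is that the intent is clear. The sentence is about incidence, the aim is new cases, baseline tests are scheduled, and newly diagnosed HIV is identified separately. Intent-to-treat means analysis by assigned arm and does not require including women who cannot have the event. An analysis plan that is not shown might define the at-risk set. It is also fair that the sentence introduces these as secondary analyses, although the same section lists HIV and HCV incidence among the primary outcomes.

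The point on intent-to-treat stands: inclusion of all women is inferred from that sentence together with the missing restriction. The rest does not remove the problem. The article does not leave the definition open; it fixes one, and that one contradicts the aim. The power argument, which treats prevalence as if it added power, shows that this is more than loose wording.

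A reader might go further and infer that the primary STI endpoint has the same defect through syphilis. The documents do not support that. The primary analysis is of an incident STI, with treatment before randomization, and it can also include self-reported infections treated elsewhere. Nothing states that the syphilis assay stays positive after treatment, and no syphilis prevalence is given. A persistent share of 10% would already use up the listed 10% prevalence for all STIs. What remains is narrower: only active forms are treated, so nothing in the text stops a repeat positive screen in a woman without active disease from being counted.

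**Conclusion.** The concern holds for HIV and HCV. As written, the coding counts existing infections as new and contradicts the stated aim.

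Its size depends on incidences the documents do not give. A true RR of 0.30 becomes 0.97–0.99 for HCV under the two assumed pairs, so HCV is in effect untestable as defined. For HIV it becomes 0.60–0.92, depending on prevalence and incidence. A reader might infer that the HIV effect also all but vanishes, but that is approached only when 28% prevalence is combined with the lower assumed incidence.

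The claim of more than 80% power for HIV and HCV is unsupported under either coding in these scenarios.

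For syphilis there is an unclosed gap in the endpoint definition. Its effect on the primary analysis is unknown. The illustrative shares show attenuation, not loss of the effect.

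**What to change.** - Define incident HIV and incident HCV as a first positive follow-up test among women negative at baseline, compared by assigned arm.
- Withdraw the statement that power exceeds 80% for HIV and HCV, or restate it from the expected number at risk and an explicit incidence assumption. State whether the 28% baseline prevalence belongs to HIV or to STIs.
- Define incident syphilis against the baseline screen and the confirmatory result, so that a repeat positive screen alone is not an event. Counting seroconversion only would be simpler but would miss re-infection in women who were screen-positive at baseline.

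The HIV and HCV change needs no new data, because baseline tests are already scheduled. Its cost is a smaller analysis set (about 35 per arm for HCV and 101–126 for HIV) and a less favourable stated power. These results should be reported as estimates with confidence intervals, and a null result should not be read as evidence of no effect. The syphilis rule depends on the confirmatory results being available to the study.

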#### Power and sample size

Power and sample size considerations for this proposal prioritized sufficiently powering the study to detect intervention effects on incidence for the following biological outcomes: STIs (syphilis, gonorrhea, trichomoniasis, chlamydia, and mycoplasma), HIV and hepatitis C virus (HCV). Using baseline prevalence estimates from our prior work in similar populations (e.g., 10%, 28%, and 75%, for STIs, HIV, and HCV, respectively) [29], we conservatively focused on the least prevalent of the three biological outcomes of interest, STIs. We noted that if we were sufficiently powered to estimate intervention efficacy for the least prevalent outcomes, we would also be sufficiently powered to detect intervention effects for the others. Using these prevalence estimates, we determined a range of plausible incidences based on our experience in similar settings. We first calculated crude (unadjusted for clustering by cohort) using a conventional approach to detect differences in a binary outcome (e.g., incidence) in two groups assuming an *α*-level of 0.05 for a two-sided hypothesis test of an overall intervention effect. Crude sample size estimates were then inflated by the “variance inflation factor” as described in Donner and Klar [30], to account for the likely correlation of outcomes induced by the study’s cluster randomized design. Finally, we adjusted 20% attrition over the 15-month follow-up. We considered scenarios of modest (intraclass clustering coefficient (ICC) equal to 0.005) and moderate (ICC = 0.01) clustering effects. In summary, we determined that randomizing 350 women in equal proportions to each intervention (175 to HIVRR and HIVRR+MF) would ensure that 80% power to detect true relative risks of 0.25 and ICC = 0.01. This attrition and clustering adjusted sample size corresponds to detecting STI incidence relative risks (RR) equal to 0.25 comparing women randomized to HIVRR+MF to HIVRR alone, where the assumed STI incidence over the study follow-up period is 0.043 and 0.144, respectively. In these calculations, the assumed incidence in HIVRR alone of 0.144 represents a decrease of approximately 40% from the estimated baseline prevalence of 28% from our prior work in this population [29]. Because the other biological outcomes of interest are more prevalent, we expect to have greater than 80% power to detect similar intervention effects.

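### The sample-size paragraph contradicts itself on relative risk (0.25 against 0.30), STI baseline prevalence (10% against 28%) and the size of the assumed fall (40% against 49%)

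*Protocol article*

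**What the plan says.** All the figures are in the protocol article, under Power and sample size.

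- Test: a significance "level of 0.05 for a two-sided hypothesis test of an overall intervention effect".
- Claim: 350 women, 175 per arm, "would ensure that 80% power to detect true relative risks of 0.25 and ICC = 0.01", after inflation for clustering and for 20% attrition.
- Effect: the same sample size is then said to correspond to "detecting STI incidence relative risks (RR) equal to 0.25 comparing women randomized to HIVRR+MF to HIVRR alone", and "the assumed STI incidence over the study follow-up period is 0.043 and 0.144, respectively" (HIVRR+MF first, HIVRR alone second).
- Base rates from prior work: "10%, 28%, and 75%, for STIs, HIV, and HCV, respectively". STIs are chosen for sizing because they are the least prevalent of the three.
- Origin of the control rate: 0.144 "represents a decrease of approximately 40% from the estimated baseline prevalence of 28" per cent, citing the same prior work.
- Other outcomes: HIV and HCV are expected to have more than 80% power because they are more prevalent than STIs.

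**The concern.** Three pairs of statements cannot all be true.

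1. The relative risk of 0.25 does not match the two incidences given for it.
2. The control STI incidence is described as a fall from 28%, which the same paragraph lists for HIV. The prevalence listed for STIs is 10%, and 14.4% cannot be a decrease from 10%.
3. The fall from 28% to 14.4% is not about 40%.

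This is the article's only power statement. It supports the analysis that the Data analysis section names as primary, the logistic GEE for an incident STI. A reader who later has to interpret a null result needs to know which effect, at which control rate, the trial had 80% power to detect. The mismatch in relative risk has little effect on this. The mismatch in base rate could have a large one, because power depends strongly on control incidence. It also touches the HIV and HCV claim, which relies on STIs being the least prevalent outcome.

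**Working it through.** **Direct arithmetic**
- 0.043 / 0.144 = 0.299. A relative risk of 0.25 on 0.144 would be 0.25 × 0.144 = 0.036.
- The odds ratio is (0.043/0.957) / (0.144/0.856) = 0.267, so 0.25 is not a mislabelled odds ratio either.
- 1 − 0.144/0.28 = 48.6%. A 40% fall from 28% would be 0.6 × 0.28 = 0.168.
- 0.144/0.10 = 1.44, so against the listed STI prevalence 0.144 is 44% higher.

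**Reproducing 350**

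Inputs from Power and sample size: two-sided 0.05, 80% power, 0.144 against 0.043, ICC 0.01, 20% attrition, 175 per arm. Cohort size: 6 to 8 (Group assignment and randomization); 350 women in about 50 cohorts (Abstract) gives a mean of m = 7.

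Crude n per arm = [1.96·√(2p̄(1−p̄)) + 0.842·√(p₁(1−p₁)+p₂(1−p₂))]² / (p₁−p₂)², with p̄ = 0.0935:
- (1.96 × 0.4117 + 0.842 × 0.4055)² / 0.101² = 129.2, rounded up to 130.
- Design effect = 1 + (7−1) × 0.01 = 1.06.
- 130 × 1.06 / 0.80 = 172.25, rounded up to 173 per arm, 346 in total (342 for m = 6, 348 for m = 8).
- Retained per arm: 175 × 0.80 = 140. Effective n = 140/1.06 = 132. Power = 80.9% (81.2% for m = 6, 80.5% for m = 8).

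So 350 and 80% follow from the stated pair of incidences, whose relative risk is 0.30.

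**Other readings of the paragraph** (same formula, m = 7, ICC 0.01, no continuity correction)

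| Control vs HIVRR+MF | Basis | RR | Total for 80% power | Power with 350 |
|---|---|---|---|---|
| 0.144 vs 0.043 | stated pair | 0.30 | 346 | 81% |
| 0.144 vs 0.036 | stated RR on stated control rate | 0.25 | 292 | 87% |
| 0.172 vs 0.043 | stated RR and stated treatment rate | 0.25 | 240 | 93% |
| 0.168 vs 0.042 | true 40% fall from 28% | 0.25 | 244 | 92% |
| 0.06 vs 0.015 | assumed: 40% fall from 10% | 0.25 | 740 | 49% |
| 0.06 vs 0.018 | assumed: 40% fall from 10% | 0.30 | 884 | 42% |

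The 6% control rate in the last two rows is an assumption made here. It does not appear in the article.

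**Continuity correction.** The article does not say whether one was used. With it, 0.144 vs 0.036 needs 127 per arm crude, or 338 in total at m = 7 (334 to 340 for m = 6 to 8), with 82% power at m = 7. The stated pair would then need 149 per arm crude, 396 in total, with 74% power.

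**The case against.** The strongest reply is that the calculation is defined well enough. An explicit pair of incidences, the significance level, ICC, attrition and allocation are all given, and they reproduce 350 and 80%. On that reading only the label 0.25 is wrong, and it errs safely: at a control rate of 0.144, a true relative risk of 0.25 has more power than claimed. This stands.

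It also stands that 10% prevalence would not by itself make 0.144 implausible. Prevalence is measured once. The outcome is cumulative over 15 months, covers five infections, is tested at months 9 and 15, and adds self-reported STIs treated elsewhere. Cumulative incidence can exceed point prevalence, in which case only the description of 0.144 as a decrease would be wrong. In addition, enrolment closed in July 2017, so the sample size can no longer change, and the promised 95% confidence intervals limit the risk that a null result is over-read.

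Two stronger readings are tempting and should be resisted. A reader might infer that 350 proves a relative risk of 0.30 was intended. It does not, because with a continuity correction 0.25 on 0.144 also lands near 350. A reader might also infer that the trial is underpowered. That would require a 6% control rate, which the article never states; it gives no general rule of a 40% fall and refers to a range of plausible incidences drawn from experience. Even in that case, 49% is about three-fifths of the claimed 80%.

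None of this removes the contradictions, and no other section of the article resolves them.

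**Conclusion.** The paragraph is wrong as written on three figures: a relative risk of 0.25 against 0.30, an STI base of 10% against 28%, and a fall of about 40% against 49%. The sample size of 350 and the 80% power are not shown to be wrong. They hold for 0.144 against 0.043 without a continuity correction, which makes 0.30 the likeliest intended relative risk, subject to the authors confirming their method.

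The 10%/28% conflict is the part with possible substance. Which figure belongs to STIs depends on the cited prior work, which is not available here. If it is 10%, the article's explanation of 0.144 fails and the control rate needs another basis. The 42% to 49% power figures show how much could depend on that, under an assumed 6% control rate, m = 7 and ICC 0.01. They do not demonstrate a shortfall. The claim of more than 80% power for HIV and HCV rests on the prevalence ordering that the 28% figure puts in doubt.

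**What to change.** Restate one coherent set of figures:

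1. The two incidences, the relative risk that matches them (0.30 if the pair 0.144 and 0.043 stands) and the power for that pair (81% at m = 7, ICC 0.01, 20% attrition), saying whether a continuity correction was used.
2. The STI prevalence actually observed in the prior work, correcting whichever of 10% and 28% is misplaced, with the right percentage change (49% for 28% to 14.4%).
3. If 10% is the STI prevalence, either a justification of 0.144 as 15-month cumulative incidence on other grounds, or a statement that power would be lower, with the assumed control rate and the resulting figure.
4. A recheck of the statement on HIV and HCV power once the ordering is settled.

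The cost is rewording one paragraph and looking up one figure in the prior work. No participants are added and no analysis changes, though a stated power figure may become less favourable.

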## Methods/design

This study uses a cluster randomized controlled trial (c-RCT) to evaluate a combination HIVRR and microfinance (MF) intervention among FSW who use drugs in Kazakhstan. The study compares two arms: a combination HIVRR+MF intervention treatment arm and a control arm, which receives the HIVRR component alone. The study assesses outcomes over a 15-month period, which encompasses up to 3 months of intervention activities, and 12 months of follow-up. Study recruitment and enrollment began in May 2015, and follow-up data collection will be completed in October 2018.

The theoretical framework for the study is shown in Fig. 1. The primary aim of the study is to test whether participants assigned to the combined HIVRR+MF condition have improved outcomes on a number of indicators, as compared to those assigned to the HIVRR condition. These indicators include: (1) a lower cumulative incidence of biologically confirmed STIs (syphilis, gonorrhea, trichomoniasis, chlamydia and mycoplasma), (2) a lower rate of new HIV and hepatitis C virus (HCV) cases, (3) a greater decrease in the number of unprotected vaginal and anal sexual acts and a greater increase in the proportion of protected sexual acts with both regular and paying partners, (4) a reduction in the proportion of unsafe injection acts for those participants who inject drugs, and (5) a lower proportion of monthly income from sex work. These outcomes are summarized in Table 1.

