### Study procedures

The study design is summarized in the Consolidated Standards of Reporting Trials (CONSORT) diagram (Fig. 2) and in the Standard Protocol Items: Recommendations for Interventional Trials (SPIRIT) schedule (Fig. 3 and Additional file 1). We expect to enroll 350 participants in the intervention over the course of 2 years, and to follow them up over 15 months post randomization. Prior studies in Kazakhstan have yielded retention rates of 88% [29]; we expect to retain 80% (*n* = 280) of participants at their month-15 follow-up assessment.

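### The claim of more than 80% power for HIV and HCV incidence is unsupported and runs the wrong way: higher baseline prevalence of a lasting infection leaves fewer women at risk

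*Protocol article*

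**What the plan says.** The Power and sample size section gives baseline prevalences of 10%, 28% and 75% for STIs, HIV and HCV. It picks STIs as the least prevalent outcome and argues that, with enough power for that one, "we would also be sufficiently powered to detect intervention effects for the others". It closes with "Because the other biological outcomes of interest are more prevalent, we expect to have greater than 80% power to detect similar intervention effects". No HIV or HCV incidence, at-risk number or power calculation is given.

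The endpoint itself is incident infection: the primary aim in Methods/design includes "a lower rate of new HIV and hepatitis C virus (HCV) cases". Data analysis names HIV and HCV incidence in its opening list of primary outcomes. It later places both under secondary analyses, as binary indicators of a positive test over follow-up.

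**The concern.** The argument treats baseline prevalence as if it were the event rate. Power for a comparison of new infections depends on how many women are uninfected at the start and how many of them become infected. For a lasting infection, a higher prevalence at a given incidence and relative risk means fewer women at risk and less power.

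The protocol confirms that the at-risk group shrinks. HIV and HCV status are not eligibility criteria (Participant characteristics), and HIV-positive women are enrolled and followed (Assessments). Curable STIs are treated before randomization so that later ones count as incident. HIV and HCV have no such step: treatment is described as limited or not widely available, and HCV is tested with an anti-HCV assay.

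At stake is how a null result would be read. A finding of no difference in HIV or HCV would be reported from comparisons that the published protocol describes as more than 80% powered.

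**Working it through.** **Inputs, all from the protocol article**
- Test: "assuming an *α*-level of 0.05 for a two-sided hypothesis test of an overall intervention effect".
- STI incidences for HIVRR+MF and HIVRR: "where the assumed STI incidence over the study follow-up period is 0.043 and 0.144, respectively". Their ratio is 0.043/0.144 = 0.299, whereas the text states a relative risk of 0.25, so both are carried below.
- Attrition: "Finally, we adjusted 20% attrition over the 15-month follow-up". Study procedures agrees: "we expect to retain 80% (*n* = 280) of participants at their month-15 follow-up assessment", that is 140 per arm.
- Cohorts of six to eight women and ICC 0.01. At size 7 the design effect is 1 + 6 × 0.01 = 1.06.

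**Formula.** With n effective women per arm, control risk p1, intervention risk p2 and their mean p:

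power = Φ{ [ |p1 − p2|√n − 1.96√(2p(1−p)) ] / √(p1(1−p1) + p2(1−p2)) }

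**Step 1: reproduce the STI sizing.** The matching sample-size formula for 0.144 versus 0.043 gives 130 per arm. Then 130 × 1.06 / 0.8 = 172.25, rounded up to 173 per arm or 346 in total. Cohort sizes 6 and 8 give 342 and 348, against the stated 350. With n = 140/1.06 = 132.1, power is Φ{(0.101 × 11.49 − 1.96 × 0.4117)/0.4055} = Φ(0.87) = 80.9%. The method therefore matches the plan's own calculation.

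**Step 2: restrict to women at risk.**
- HIV at 28%: 140 × 0.72 = 100.8 per arm, or 95.1 effective.
- HCV at 75%: 140 × 0.25 = 35 per arm, or 33.0 effective.

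**Step 3: power with the same incidence and effect as for STIs.** For 0.144 versus 0.043:
- HIV: Φ{(0.101 × 9.75 − 0.807)/0.4055} = Φ(0.44) = 67%.
- HCV: Φ{(0.101 × 5.75 − 0.807)/0.4055} = Φ(−0.56) = 29%.

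Other control incidences in baseline-negative women (all but 14.4% are assumptions), with relative risk 0.30 first and 0.25 second:

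| Control incidence | HIV, 28% prevalence | HCV, 75% prevalence |
|---|---|---|
| 1% | 9%, 10% | 5%, 6% |
| 2% | 13%, 15% | 7%, 8% |
| 5% | 28%, 32% | 12%, 14% |
| 14.4% | 67%, 74% | 29%, 33% |
| 20% | 83%, 89% | 39%, 45% |

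The control incidence that gives 80% power is 16.3% (relative risk 0.25) to 18.9% (0.30) for HIV, and 38.7% to 43.5% for HCV.

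**Step 4: enrolment needed at 0.144 versus 0.043.** HIV: 172.25/0.72 = 239.2, so 480 women in total. HCV: 172.25/0.25 = 689 per arm, so 1,378 in total.

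**Step 5: sensitivity.**
- Removing the design effect altogether, at 0.144 and relative risk 0.30, gives 70% for HIV and 30% for HCV.
- If the indicator of a positive test were taken literally and baseline positives counted as outcomes, the HIV risks become 0.28 + 0.72 × 0.144 = 0.384 and 0.28 + 0.72 × 0.043 = 0.311. For HCV they become 0.786 and 0.761. With 132.1 effective women per arm, power is about 24% and 7%.
- With only a few expected control events (about one for HIV at 1%, about two for HCV at 5%) the normal approximation is unreliable. The low-incidence figures are rough, and an exact test would give less power.

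**The case against.** **HIV incidence is unknown.** A reader might infer that HIV power is very low, or that the trial could not detect even a 70–75% reduction in HIV. The protocol does not support that. The figures of 9–32% rest on an assumed incidence of 1–5%. At the only control incidence the protocol states, HIV power is 67–74%, and at 20% it would exceed 80%. This objection stands: for HIV the claim is unsupported, and how far it misses depends on a figure that is not given. It does not help HCV.

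**The prevalence labels conflict.** The section first attaches 28% to HIV and 10% to STIs, then uses 28% as the base from which the STI incidence of 0.144 is derived. If the two labels were swapped, 140 × 0.90 = 126 women per arm would be at risk for HIV, and power at 14.4% would be 77% (relative risk 0.30) or 83% (0.25). This also stands, so the HIV at-risk number is provisional. It does not rescue the reasoning, because HIV would then not be more prevalent than STIs.

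**HIV and HCV are secondary, with confidence intervals already promised.** This is partly right. Data analysis makes incident STI the primary analysis and commits to 95% intervals, but it also lists HIV and HCV incidence as primary, and the power claim covers them regardless.

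**Cost-effectiveness.** A reader might infer that low power undermines the cost-effectiveness results. The documents do not show that: the Cost-effectiveness analyses section constructs transmissions averted from risk-behaviour frequencies and per-act probabilities through a Bernoulli process model.

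**Conclusion.** The concern holds in this form. Prevalence is the only ground offered for the power claim, and for lasting infections it points in the opposite direction. For HCV the claim is clearly wrong at the stated 75% prevalence unless roughly two in five negative control women became infected during follow-up. For HIV, more than 80% is not shown; it would require an incidence above the one assumed for STIs if 28% is the right prevalence.

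These results assume 20% attrition spread evenly over baseline status, a design effect of 1.06, and relative risks of 0.25–0.30. The STI sample size reproduces and is unaffected.

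**What to change.** 1. Delete both sentences that claim adequate power for HIV and HCV.
2. Define these endpoints as new infections among women negative for that infection at baseline.
3. State that the trial was sized for STI incidence only, and not for HIV or HCV.
4. Label HIV and HCV incidence as secondary throughout, including the primary aim and the opening of Data analysis, and report them with confidence intervals.
5. Reconcile the 10% and 28% labels before quoting an HIV at-risk number: about 202 retained women (280 × 0.72) at 28%, or 252 (280 × 0.90) at 10%. For HCV it is 70 (280 × 0.25).

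The cost is wording and the loss of a favourable power claim. Sample size, primary STI analysis and conduct do not change.
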